### Adverse Events

Adverse events will be measured and recorded during the study. The adverse events may include incidents such as skin reactions (e.g., blisters or rashes) from the prefabricated orthoses or heel lifts.

### Analysis

The intervention factors will be examined over time on the primary and secondary outcome measures using Generalised Estimating Equations. This approach is suitable for analysis of longitudinal data and has been shown to produce unbiased effect estimates with appropriate precision in the presence of missing data (missing completely at random, missing at random or missing not at random) without the need for data imputation techniques and does not involve list wise deletion of participant data where missing data is present [41]. The analysis will be undertaken to examine the main effects of the two intervention factors, however, if a significant "shoe orthoses by footwear" interaction term is identified, simple effects will be focused upon. The analysis will follow the intention-to-treat principle.

A follow-up per-protocol analysis will be conducted to account for participants who do not adhere to their allocated treatment protocol. However, such analyses will be described as being exploratory and will not be the focus of the resulting manuscript

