### Sample size

It is considered that a minimum clinically important change in the Oxford Ankle Foot Questionnaire in any domain is 7 points and that based on previous work, the maximum standard deviation in any domain is 6 points [36]. Given this experiment has 1 pre-intervention measure and 3 post-intervention measures, a sample size of n = 27 per factorial trial cell (i.e., total trial n = 108) will have >90% power to detect a significant difference of 7 points in any simple contrasts undertaken, assuming a correlation between assessment points within individual participants is r = 0.7. To account for 15% drop outs and incomplete assessments, a total of n = 124 will be recruited.

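### The protocol says GEE is unbiased under any missing-data mechanism, MNAR included, without imputation; this is false, and outcome-related drop-out could bias the result

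*Protocol article*

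**What the plan says.** The protocol article, Analysis, names one method for every outcome: "The intervention factors will be examined over time on the primary and secondary outcome measures using Generalised Estimating Equations". It says this method "has been shown to produce unbiased effect estimates with appropriate precision in the presence of missing data" and then lists the mechanisms covered: "presence of missing data (missing completely at random, missing at random or missing not at random) without the need for data imputation techniques". It gives no working correlation, weighting or imputation. The per-protocol analysis in the same section deals with non-adherence, not with missing outcomes.

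Two other sections bear on the point. Sample size makes an allowance for loss: "To account for 15% drop outs and incomplete assessments, a total of n = 124 will be recruited". Procedure sets steps to limit loss: text reminders, a telephone call to rebook, then the primary questionnaire by post, then its completion by telephone. The postal and telephone completion is for the Oxford questionnaire only, not for the Faces pain scale or the Lunge Test.

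**The concern.** The sentence claims a property that GEE does not have, and offers it as the reason imputation is not needed. It is a wrong statement about the validity of the primary analysis, not a detail left to another document.

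At stake is how the result will be read. A reader who trusts the sentence will take the estimate and its confidence interval as robust to selective drop-out. Such drop-out is plausible. Children whose pain has gone have little reason to return, and those doing badly may go elsewhere. It could also differ by arm: the Conclusion concedes that patients are not blinded and that the footwear factor sets an active level against an inactive one, and one level of that factor receives free shoes.

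**Working it through.** **Inputs from the protocol.** From Sample size: "minimum clinically important change in the Oxford Ankle Foot Questionnaire in any domain is 7 points"; "the maximum standard deviation in any domain is 6 points"; within-child correlation 0.7; 27 per cell (108 in total); 15% loss. From Procedure: baseline and months 1, 2 and 3.

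**Assumptions of mine.** Two-sided alpha 0.05; normal outcome with equal correlations; a separate mean for each arm at each visit; permanent drop-out after baseline; 15% of outcomes missing at month 3; and the drop-out models below, since the protocol gives none.

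**1. The plan's own figures.** For one post-treatment comparison with 27 per cell, SE = 6 × √(2/27) = 1.63 and 7/1.63 = 4.29. Power is Φ(4.29 − 1.96) = 99.0%, in line with the stated >90%. The recruitment target is 108 × 1.15 = 124.2, hence 124. These figures reproduce and are not in dispute here.

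**2. When the claim is true.** Unweighted GEE sets weighted residuals of the observed data to zero.
- MCAR, or missingness that depends only on modelled covariates: observed residuals average zero, so the estimate is consistent.
- MAR depending on earlier outcomes: they generally do not average zero. Weighting, imputation or, for a normal-type outcome, a correct working correlation repairs this.
- MNAR: the observed data do not identify the missing part, so no method is unbiased without untestable assumptions.

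**3. Size by hand.** Under independence working correlation, the month-3 estimate is the difference in observed means. In each arm, observed mean − true mean = p × (observed mean − missing mean), where p is the fraction missing. If p = 0.15 and missing children differ from observed children by 4 points, each arm shifts by 0.15 × 4 = 0.6. Shifts in the same direction cancel. Shifts in opposite directions add to 1.2.

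**4. Simulation, 15% missing.** Two arms, 60,000 children per run, drop-out log-odds changing by 1 per SD of outcome (odds ratio e¹ = 2.7). Monte Carlo noise is about 0.05 to 0.1. Month-3 estimates:

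| Drop-out | True effect | Independence | Exchangeable |
|---|---|---|---|
| MCAR | 7 | 6.95 | 6.93 |
| MAR, same direction in both arms | 7 | 6.98 | 7.07 |
| MAR, same direction in both arms | 0 | −0.03 | −0.04 |
| MAR, opposite directions | 7 | 8.20 | 7.04 |
| MAR, opposite directions | 0 | 1.20 | 0.02 |
| MNAR, same direction in both arms | 7 | 6.72 | 6.97 |
| MNAR, same direction in both arms | 0 | 0.05 | 0.02 |
| MNAR, one arm only | 7 | 7.58 | 7.13 |
| MNAR, opposite directions | 7 | 8.48 | 7.54 |
| MNAR, opposite directions | 0 | 1.40 | 0.48 |

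**5. Stronger drop-out.** A slope of 0.25 per point is 0.25 × 6 = 1.5 per SD (odds ratio e^1.5 = 4.5). With independence, the absolute bias was about 0.6 to 0.7 (MAR, same direction, true effect 7), 1.6 (MAR, opposite directions) and 1.0 to 1.8 (MNAR). With exchangeable correlation it was about 0 under MAR and 0.3 to 0.6 under MNAR. When the true effect was 0 and drop-out was the same in both arms, it was near 0 with either structure. The sign follows which arm loses which children: the estimate was too high in the opposite-direction rows above and too low in these runs.

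**6. Scale.** A main effect at one visit compares 108/2 = 54 children per level, so SE = 6 × √(2/54) = 1.15. A bias of 1.20 at a true effect of 0 is 1.20/1.15 = 1.04 SE. The false-positive rate becomes Φ(1.04 − 1.96) + Φ(−1.04 − 1.96), about 18% instead of 5%. This is illustrative and applies to independence working correlation only.

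**The case against.** The strongest defence concedes the sentence and disputes its consequences.

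- *Retrieval.* Procedure lets the primary questionnaire be completed without attending, which directly targets children who feel better and stay away. The 15% is also a recruitment allowance for drop-outs and incomplete assessments, not a forecast of primary outcomes missing at month 3 after retrieval. This stands. A reader might infer that the trial has no safeguard, and the protocol does not support that. But retrieval does not reach the two secondary outcomes, to which the same claim is applied, and says nothing about data still missing.
- *Working correlation.* The larger biases come from independence, and the protocol names no structure. With a correct exchangeable correlation, GEE did as well as a correctly specified likelihood model in these settings. This stands, so the contrast is not GEE against mixed models. Under MNAR, bias remained even with the correct structure.
- *Drop-out model.* The slopes are strong, and the largest biases need the two arms to lose opposite kinds of children, which the protocol does not suggest. This stands, and it is why the size is given as a range.
- *Unseen documents.* A separate analysis plan may specify sensitivity analyses, and saying imputation is not needed does not forbid it. This also stands: the absence of a sensitivity analysis is not the finding. But no other document can make the sentence true.

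**Conclusion.** The point holds as a false statement about the main analysis method: GEE is not unbiased under MNAR, and in general not under MAR.

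Outcome-related drop-out could therefore bias the result. At an assumed 15% missing at month 3, with SD 6, correlation 0.7 and strong assumed drop-out slopes, the bias lies between 0 and about 1.8 points under independence. With a correct exchangeable correlation it is about 0 under MAR and at most about 0.6 points under MNAR. That compares with the 7-point target.

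A reader might go further and conclude that the primary result would be biased. The protocol does not support this: size and direction depend on a drop-out pattern and a working correlation it does not state, and in several plausible settings the bias is negligible.

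**What to change.** 1. Delete the claim and state the missing-data assumption under which the primary analysis is valid.
2. Make that analysis valid under MAR. Two routes are adequate: keep GEE with inverse-probability weighting or multiple imputation, or use a likelihood-based repeated-measures model. Neither removes MNAR bias.
3. Add a delta-adjusted MNAR sensitivity analysis. For example, shift the missing values in one arm by up to the 7-point important change. At 15% missing this moves the estimate by 0.15 × 7 = 1.05 points, so an estimate of 7 would become 5.95.
4. Apply the same wording to the Faces pain scale and the Lunge Test, which the postal and telephone completion does not cover.

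The cost is revised text and a little more analysis code, with no new data and no change to trial conduct.

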### Sample size

It is considered that a minimum clinically important change in the Oxford Ankle Foot Questionnaire in any domain is 7 points and that based on previous work, the maximum standard deviation in any domain is 6 points [36]. Given this experiment has 1 pre-intervention measure and 3 post-intervention measures, a sample size of n = 27 per factorial trial cell (i.e., total trial n = 108) will have >90% power to detect a significant difference of 7 points in any simple contrasts undertaken, assuming a correlation between assessment points within individual participants is r = 0.7. To account for 15% drop outs and incomplete assessments, a total of n = 124 will be recruited.

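### The drop-out allowance is miscalculated: 124 recruits less 15% leave about 105 children, not the stated 108. This is a minor correction that does not threaten power.

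*Protocol article*

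**What the plan says.** All the figures are in the Sample size section of the protocol article. The effect size is set by the statement that "a minimum clinically important change in the Oxford Ankle Foot Questionnaire in any domain is 7 points", and the variability by the statement that "the maximum standard deviation in any domain is 6 points". The calculation is described as "assuming a correlation between assessment points within individual participants is r = 0.7". The evaluable number is given as "a sample size of n = 27 per factorial trial cell (i.e., total trial n = 108", and the article says this number "will have >90% power to detect a significant difference of 7 points in any simple contrasts undertaken".

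The recruitment total follows: "To account for 15% drop outs and incomplete assessments, a total of n = 124 will be recruited". The Method part of the Abstract repeats the figure of 124. The article states no other retention rate, reserve or replacement rule.

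**The concern.** The evaluable target, the loss allowance and the recruitment total form one linked statement, so any two of them should give the third. Here they do not: taking 15% off 124 does not return 108. A trial that recruited exactly as planned, and lost exactly the planned share of children, would report fewer evaluable children than its own protocol promised.

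What is at stake is the accuracy of a published sample-size figure, against which the final report will be compared. Whether power is also at stake has to be checked separately, and that is done below.

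**Working it through.** **Inputs from the Sample size section:** evaluable target 27 per cell, 108 in total over four cells; loss allowance 15%; recruitment total 124, which is 124 / 4 = 31 per cell; difference 7 points; SD 6 points.

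**Assumption:** two-sided alpha of 0.05, which the article does not state. It is used only in step 5; the inflation arithmetic does not depend on it.

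**1. Reproduce the stated total.** Target × (1 + loss) = 108 × 1.15 = 124.2, rounded to 124. Per cell, 27 × 1.15 = 31.05, rounded to 31. The stated figure is reproduced by adding 15% to the target.

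**2. Apply the loss to the children recruited.** Target / (1 − loss) = 108 / 0.85 = 127.06. Rounded up to four equal cells this is 128 (32 per cell), and 128 × 0.85 = 108.8, which covers 108. The gap to 124 is about 3 recruits before rounding and 4 after it.

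**3. Work forward from 124.** 124 × 0.85 = 105.4, or 31 × 0.85 = 26.35 per cell. The shortfall against 108 is 2.6 children, or 2.6 / 108 = 2.4%. This count treats every child in the 15% as contributing nothing.

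**4. Loss at which 124 leaves exactly 108.** (124 − 108) / 124 = 16 / 124 = 12.9%.

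**5. Effect on power for a simple contrast between two cells.** A single measurement per child is used, which ignores any gain from the repeated measures. By the normal approximation, power = Φ(7 / (6 × √(2/n)) − 1.96).

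| n per cell | 7 / (6√(2/n)) | minus 1.96 | power |
|---|---|---|---|
| 27 | 4.287 | 2.327 | 99.0% |
| 26.35 | 4.235 | 2.275 | 98.9% |
| 26 | 4.207 | 2.247 | 98.8% |

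A t-test calculation gives 98.8%, 98.6% and 98.5% for the same three sizes.

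**6. Cell size that gives 90% power.** n = 2 × (1.96 + 1.2816)² × 6² / 7² = 2 × 10.51 × 0.735 = 15.4, so 16 per cell by the normal approximation and about 17 by the t-test. Both lie far below 26.

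**7. A less favourable case.** Suppose the SD were as large as 7.93, the value at which 27 per cell gives exactly 90% power. Then 26.35 per cell would give 89.3%, so the shortfall would cost under one percentage point.

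**The case against.** Three points can be made on the other side.

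- **The 15% could have been meant as a share of the evaluable target.** On that reading 124 is right. But the sentence speaks of drop-outs, and children drop out of the group recruited. No other base is named, so the sentence would need rewording in either case.

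- **Not every child in the 15% is lost.** The allowance covers incomplete assessments as well as drop-outs. The Analysis section plans generalised estimating equations, which do not discard a child because some visits are missing. The Procedure section adds postal and then telephone completion of the primary questionnaire after a missed appointment. This point stands as to consequence: 105 is the count if all 15% are lost completely, and because the article does not split the 15%, the real shortfall could be smaller or nil. It does not repair the formula, since the sentence itself treats incomplete assessments as something to recruit extra children for.

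- **The discrepancy is small.** This also stands. Unrounded, 127.06 is only 2.5% above 124 (3.06 / 124). But rounding does not explain the gap, because a different formula was used.

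A reader might go further and infer that the power claim needs 108 children, or that the design can tolerate no more than 12.9% loss. The article does not support either. It says that 27 per cell gives more than 90% power, not that 27 is the minimum. On its own inputs, power stays above 90% down to about 17 per cell, which is 68 children, or a loss of 56 / 124 = 45%. The 12.9% limit applies only to keeping the figure of 108.

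**Conclusion.** The stated figures are inconsistent, and the cause is identifiable: 15% was added to the target where the target should have been divided by 0.85. With 15% lost completely, 124 recruits leave about 105 children (26.35 per cell), 2.6 short of the stated 108.

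This is a minor arithmetic correction. It changes no design decision, error rate or planned analysis. The claim of more than 90% power remains true, at about 99% with either cell size, given the stated 7 points and SD of 6 and an assumed two-sided alpha of 0.05. The error gives no ground for calling the trial underpowered.

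**What to change.** Change one sentence in the Sample size section, in one of two ways:

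- **Preferred:** keep 124 and the 15% allowance, and state that if all 15% were lost completely about 105 children (about 26 per cell) would remain, with power for simple contrasts still above 90%. Add that children with partial follow-up stay in the analysis.
- **Alternative:** if 108 is to be kept as the evaluable number, state that 124 covers a loss of about 13%. This is the weaker choice, because it fits the loss rate to the recruitment total and nothing in the article supports 13% as an expected rate.

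Either way the 124 in the Abstract stands, no extra children are recruited, and the cost is one edited sentence. A total of 128 would be required only to hold both 15% and 108, and the power figures give no reason to insist on that.

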### Ethical Consideration

Ethical approval for this study has been obtained by the Southern Health Human Research Ethics Committee HREC Ref: 09271B. Registration of this randomised control trial has been completed with the Australian New Zealand Clinical Trial Registry ACTRN12609000696291.

## Conclusion

Posterior heel pain associated with a clinical diagnosis of calcaneal apophysitis is a common disorder amongst pre-teen children. Despite this, there is presently no randomised controlled trial of clinical treatment options. This trial will provide evidence of the efficacy for some commonly used treatment options from a randomised trial for the first time. The outcomes of this trial are therefore likely to strongly influence practice guidelines and clinical care in this area.

This trial will be limited by its inability to blind outcome assessors (who are the patients' treating podiatrists) though the potential impact of this on trial results is questionable. The primary outcome measure (Oxford Foot and Ankle Questionnaire) is a patient and parent self-report measure, as is the Faces pain scale secondary outcome, hence there may be limited potential for treating podiatrists to influence these results. This trial will be limited by its inability to blind the patients receiving the treatment modalities. This is believed to more likely to affect the new footwear factor, as this compares an active to an inactive treatment level.

This trial is also limited in its ability to test all different combinations of possible treatment factors as there are several other possible treatment approaches available. The present treatment approaches were selected as they were considered by the investigators to be some of the most commonly used strategies available that were also likely to demonstrate clinical efficacy.

A paucity of research evidence supporting the theorised pathomechanics and efficacy of treatment options for a condition such as calcaneal apophysitis creates uncertainty for clinicians attempting to pursue an evidence-based treatment approach. These trials, and other similar trials, are needed to help clinicians better understand this condition and the efficacy of treatment approaches they provide.
